**\*Following cycle 4, subjects will proceed to Stem Cell Collection with potential for deferred ASCT**

| PROCEDURES                 | KRd + Dara Consolidation Cycles 5-8 |   |   |   |    |    |    |                              | KRd + Dara Maintenance Cycles 9-24 |   |   |    |    |    | End of Tx | LTFU |
|----------------------------|-------------------------------------|---|---|---|----|----|----|------------------------------|------------------------------------|---|---|----|----|----|-----------|------|
| DAY                        | 1                                   | 2 | 8 | 9 | 15 | 16 | 22 | End of Cycle 8  | 1                                  | 2 | 8 | 15 | 16 | 22 |           |      |
| Skeletal Survey            |                                     |   |   |   |    |    |    |                              |                                    |   |   |    |    |    | X         |      |
| ECG            |                                     |   |   |   |    |    |    |                              |                                    |   |   |    |    |    | X         |      |
| Physical Exam  | X                                   |   |   |   |    |    |    |                              | X                                  |   |   |    |    |    | X         |      |

| PROCEDURES                       | KRd + Dara Consolidation Cycles 5-8 |   |                 |   |                 |    |    |                              | KRd + Dara Maintenance Cycles 9-24 |   |   |                 |    |                 | End of Tx       | LTFU            |
|----------------------------------|-------------------------------------|---|-----------------|---|-----------------|----|----|------------------------------|------------------------------------|---|---|-----------------|----|-----------------|-----------------|-----------------|
| DAY                              | 1                                   | 2 | 8               | 9 | 15              | 16 | 22 | End of Cycle 8  | 1                                  | 2 | 8 | 15              | 16 | 22              |                 |                 |
| Vital Signs                      | X                                   | X | X               | X | X               | X  |    |                              | X                                  | X |   | X               | X  |                 | X               |                 |
| Height, Weight, BSA              | X                                   |   |                 |   |                 |    |    |                              | X                                  |   |   |                 |    |                 | X               |                 |
| 24-hour urine        | X                       |   |                 |   |                 |    |    |                              | X                      |   |   |                 |    |                 | X   |                 |
| Urinalysis                       |                                     |   |                 |   |                 |    |    |                              |                                    |   |   |                 |    |                 |                 |                 |
| Hematology           | X                                   |   | X               |   | X               |    |    |                              | X                                  |   |   | X               |    |                 | X               |                 |
| Serum Chemistry                  | X                      |   | X  |   | X  |    |    | X               | X                     |   |   |                 |    |                 | X               |                 |
| Pregnancy Test      | X                                   |   |                 |   | X  |    |    |                              | X                     |   |   | X  |    |                 | X  |                 |
| HBV DNA testing     | Q12W during treatment               |   |                 |   |                 |    |    |                              |                                    |   |   |                 |    |                 | X               | X  |
| Disease Assessment        |                                     |   |                 |   |                 |    |    | X               |                                    |   |   |                 |    | X  |                 | X  |
| β2-microglobulin                 |                                     |   |                 |   |                 |    |    | X                            |                                    |   |   |                 |    |                 |                 |                 |
| SPEP, UPEP          | X                                   |   |                 |   |                 |    |    | X                            | X                                  |   |   |                 |    |                 | X               |                 |
| Immunofixation – Serum and Urine | X                                   |   |                 |   |                 |    |    | X                            | X                                  |   |   |                 |    |                 | X               |                 |

| PROCEDURES                                                 | KRd + Dara Consolidation Cycles 5-8 |   |   |   |    |    |    |                              | KRd + Dara Maintenance Cycles 9-24 |   |   |    |    |    | End of Tx       | LTFU            |
|------------------------------------------------------------|-------------------------------------|---|---|---|----|----|----|------------------------------|------------------------------------|---|---|----|----|----|-----------------|-----------------|
| DAY                                                        | 1                                   | 2 | 8 | 9 | 15 | 16 | 22 | End of Cycle 8  | 1                                  | 2 | 8 | 15 | 16 | 22 |                 |                 |
| BM Aspirate/biopsy, cytogenetics, FISH        |                                     |   |   |   |    |    |    | X               |                                    |   |   |    |    |    | X  | X               |
| Quantitative Igs                                           | X                                   |   |   |   |    |    |    | X                            | X                                  |   |   |    |    |    | X               |                 |
| SFLC                                          |                                     |   |   |   |    |    |    | X               |                                    |   |   |    |    |    | X  |                 |
| Neurological Assessment                       | X                                   |   |   |   |    |    |    |                              | X                                  |   |   |    |    |    | X               |                 |
| Correlative Samples                           |                                     |   |   |   |    |    |    |                              |                                    |   |   |    |    |    | X  |                 |
| Bone marrow aspirate sample for MRD analysis  | X                                   |   |   |   |    |    |    | X                            |                                    |   |   |    |    |    | X               | X  |
| CT-PET                                        | X                                   |   |   |   |    |    |    |                              | X                                  |   |   |    |    |    | X               | X  |
| Adverse Events                                | Ongoing                             |   |   |   |    |    |    |                              |                                    |   |   |    |    |    |                 |                 |
| Concomitant Medications                                    | Ongoing                             |   |   |   |    |    |    |                              |                                    |   |   |    |    |    |                 |                 |
| Daratumumab                                   | X                                   |   |   |   | X  |    |    |                              | X                                  |   |   |    |    |    |                 |                 |

| PROCEDURES                                       | KRd + Dara Consolidation Cycles 5-8 |   |   |   |    |    |    |                              | KRd + Dara Maintenance Cycles 9-24 |   |   |    |    |    | End of Tx | LTFU            |
|--------------------------------------------------|-------------------------------------|---|---|---|----|----|----|------------------------------|------------------------------------|---|---|----|----|----|-----------|-----------------|
| DAY                                              | 1                                   | 2 | 8 | 9 | 15 | 16 | 22 | End of Cycle 8  | 1                                  | 2 | 8 | 15 | 16 | 22 |           |                 |
| Carfilzomib                         | X                                   | X | X | X | X  | X  |    |                              | X                                  | X |   | X  | X  |    |           |                 |
| Revlimid® (Lenalidomide)         | X                                   | X | X | X | X  | X  |    |                              | X                                  | X | X | X  | X  | X  |           | X  |
| Dexamethasone                       | X                                   |   | X |   | X  |    | X  |                              | X                                  |   | X | X  |    | X  |           |                 |
| Survival and New Cancer Evaluation  |                                     |   |   |   |    |    |    |                              |                                    |   |   |    |    |    |           | X               |

\* Variations of  $\pm 3$  days of the scheduled visit are permitted however doses of carfilzomib may only be rescheduled by up to 2 days (Section 6.3.1).

\*\*The KRd + Dara consolidation cycles are Cycle 5 – 8. Maintenance Cycles are 9-24.

#### Footnotes for Appendix 8

+ Documented informed consent must be obtained within  $\leq 30$  days prior to initiation of therapy.

1. Includes neuropathy history.
2. May be within 30 days planned treatment start. Includes: lateral radiograph of the skull, anteroposterior and lateral views of the spine, and anteroposterior views of the pelvis, ribs, femora, and humeri. Skeletal surveys performed outside of the 30 day window may be considered for inclusion. Please contact the Lead Principal Investigator and/or/CRA on a case-by-case basis. End of treatment skeletal survey only if clinically indicated.
3. 12-lead ECG, including QTc interval. End of treatment ECG only if clinically indicated.
4. For Day 1 of cycle 1, screening results may be used if within 7 days of treatment start.
5. Complete physical exam (including vital signs [systolic and diastolic blood pressure, respiration, pulse, oral temperature], height, weight, calculation of body surface area [BSA]) and ECOG score) required at screening and Day 1 of each cycle.

6. Systolic and diastolic blood pressure, pulse, respiration, temperature approximately 1 hour before dosing.
7. 24 hour urine total protein, urine protein electrophoresis (UPEP), and urine protein immunofixation. For subjects whose disease is being monitored through UPEP, additional post baseline 24-hour urine collections are required as indicated.
8. For subjects whose disease is being monitored through UPEP, additional post baseline 24-hour urine collections are required as indicated.
9. Hemoglobin, hematocrit, WBC with complete differential, RBCs, platelet count. Results must be reviewed before dosing.
10. Cycles 1 and 2 only and subsequent cycles as clinically indicated or per institutional standard of care.
11. Full serum chemistry panel at Screening, Days 1, 8, and 15 of Cycles 1-8, and Day 1 of Cycles 9+: sodium, potassium, chloride, bicarbonate, BUN, creatinine, glucose, uric acid, total protein, albumin, calcium, phosphorus, magnesium, total bilirubin, alkaline phosphatase, ALT, AST, LDH. Results must be reviewed before dosing in Cycles 1 and 2.
12. Abbreviated serum chemistry panel on Days 2, 9, and 16 of Cycles 1 and 2 only or as clinically indicated (e.g., risk factors for tumor lysis syndrome): sodium, potassium, chloride, bicarbonate, BUN, creatinine, glucose, uric acid.
13. Pregnancy tests for females of childbearing potential. A female of childbearing potential (FCBP) is a sexually mature female who: 1) has not had a hysterectomy or bilateral oophorectomy; or 2) has not been naturally post-menopausal for at least 24 consecutive months (i.e., menses within the preceding 24 months).
14. Pregnancy tests must occur within 10-14 days and again within 24 hours prior to prescribing lenalidomide (prescriptions must be filled within 7 days. FCBP with regular or no menstruation must have a pregnancy test weekly for the first 28 days and then every 28 days while on therapy (including breaks in therapy); at discontinuation of lenalidomide and at Day 28 post the last dose of lenalidomide. Females with irregular menstruation must have a pregnancy test weekly for the first 28 days and then every 14 days while on therapy (including breaks in therapy), at discontinuation of lenalidomide and at Day 14 and Day 28 post the last dose of lenalidomide (see Appendix 7 for Risks of Fetal Exposure, Pregnancy Testing Guidelines and Acceptable Birth Control Methods).
15. After Cycle 4, subjects who are deemed candidates for ASCT will proceed to stem cell harvest as per institutional guidelines. However, these subjects will not proceed straight to ASCT and will have cells frozen down for a potential future transplant at progression or unacceptable toxicity after stem cell harvest. After completion of stem cell harvest, subjects will resume protocol treatment.
16. Serum protein electrophoresis and urine protein electrophoresis (the latter only for those whose disease is being followed by UPEP). Subjects with baseline urine protein greater than 200 mg/24 hours must have a UPEP to confirm VGPR or better. Obtain blood for M-protein levels measured by SPEP or quantitative immunoglobulins for those subjects in whom SPEP/UPEP are felt to be unreliable (IgA type multiple myeloma), depending upon which studies were positive at baseline.
17. Disease assessments on Day 15 of Cycle 1 (only) are only for assessing onset of early response, not for definitive achievement of response.
18. Bone marrow aspirate and biopsy - quantify % myeloma cell involvement; bone marrow sample for cytogenetics and fluorescent in situ hybridization (FISH). Bone marrow aspirate and biopsy should be performed at screening and the end of D-KRD consolidation (end of cycle 8), the end of D-KRD treatment (end of cycle 24) and then yearly for up to 2 years. See sections 6.3-6.5. Repeat bone marrow biopsy/aspirate if CR is suspected and as appropriate to confirm achievement of sCR, CR, or nCR (aspirate only—biopsy not required). If CR is suspected after cycle 8, the bone marrow biopsy/aspirate must be performed at the end of

cycle 12. Bone marrow biopsy/aspirate performed outside of the 30 day window may be considered for inclusion. Please contact the Lead Principal Investigator and/or the CRA on a case-by-case basis. (Cytogenetics is required at screening only. If cytogenetics is completed at a time point other than screening, the results should be captured in eCRF)

19. SFLC repeated only to confirm CR.
20. Screening and Day 1 of every cycle. Includes neurologic exam (to detect peripheral neuropathy and/or changes in pre-existing neuropathy) and examination of clinical AEs indicative of neuropathy. Collect FACT/GOG neurotoxicity questionnaire at each time point above.
21. Peripheral blood and bone marrow aspirate samples collected at screening, end of cycle 8, time of response (to confirm complete response), end-of-treatment visit, and yearly after end of treatment for up to 2 years. Buccal mucosa swab will be collected at screening only.
22. AEs will be collected from the time of signing informed consent. 30 days following the last dose of D-KRD, patients will be considered to be off-study so no toxicities will be recorded following this period. All concomitant medications must be recorded on the concomitant medications case report form from 21 days before Day 1 through 30 days following the last dose of study drugs.
23. Assessment for disease progression in subjects who did not progress during treatment. At least every 3 months (+/- 30 days) for 5 years from safety follow-up visit (which must be 28days (+/- 3 days) post-last study treatment).
24. Lenalidomide must be prescribed through and in compliance with the Revlimid REMS® program of Celgene Corporation. Prescriptions must be filled within 7 days. Consideration should be given to prescribing lenalidomide 5 to 7 days in advance of Day 1 of each cycle to allow time for required patient and prescriber surveys, and drug shipment to patient. Any unused Revlimid® (lenalidomide) should be returned to the patient for disposition in accordance with the Revlimid REMS® program.
25. Cycles 1-8: Days 1, 2, 8, 9, 15 & 16. Cycles 9-24 Days 1, 2, 15 and 16.
26. Daily on Days 1-21 followed by a 7-day rest period every 28 days. On day coinciding with carfilzomib administration, lenalidomide should be taken at least 4 hours after the carfilzomib dose and may be self-administered at home by the subject. On days that carfilzomib is not administered, lenalidomide should be taken at approximately the same time each day.
27. Days 1, 8, 15 and 22. Dexamethasone is given between 30 minutes and 4 hours before carfilzomib on days they coincide. Dexamethasone will be dosed at 40 mg PO per week during Cycles 1-4 and 20 mg PO per week during Cycles 5-24. Cycles 9-24 represent the D-KRD Maintenance Phase of therapy and the dose of dexamethasone will remain 20 mg on days 1, 8, 15 and 22. For weeks of daratumumab injection, dexamethasone dose is split into two doses: half the dose prior to daratumumab infusion and half the dose the day after. Split weekly dosing for all other days (e.g. 10 mg on Day 1 and 10 mg on Day 2, etc.) is permitted with approval from Lead Principal Investigator. Dexamethasone given on days without carfilzomib (on Days 22 and 23 of Cycles 1-8) may be self-administered by the subject on an outpatient basis. If Day 2 of carfilzomib dosing is delayed (i.e., Day 2, 9, 16) 4 mg of dexamethasone premedication is required to be used prior to second treatment. Missed doses will not be replaced during a cycle. Missed doses of dexamethasone will not be made up. Single-agent lenalidomide maintenance therapy, is recommended using last tolerated dose of lenalidomide for 21 days in 28 day cycles after D-KRD protocol treatment (Cycles 1-24) is completed.
28. Patients will be followed for survival and development of any new cancers, at least every 3 months. Reports of any death should include date of death and specific cause (disease under study or specify other cause).
29. Evaluations at the end of Cycle 8 may be done on Day 1 of the next Cycle 9.

30. Plasmacytoma evaluation is required at screening only and may be completed as physical exam or imaging if indicated and at the treating investigator's discretion. After screening, plasmacytoma evaluation is required only for patients who have no other measurable disease and/or at investigator's discretion.
31. One bone marrow sample for central Minimal Residual Disease (MRD) analysis by NGS at Adaptive Biotechnologies will be collected from all subjects: 1) screening (sample is required for calibration of MRD by gene sequencing. In the event that a superfluous bone marrow aspirate –BMA- sample from screening was not available, slides of BMA smear or clot from a time prior to enrollment can be used), 2) end of cycle 8, 3) end of cycle 24 (EOT), 4) 1 and 2 years after EOT for all subjects; 5) any time that a bone marrow is performed as SOC to assess CR response. If CR is suspected after cycle 8, the bone marrow biopsy/aspirate must be performed at the end of Cycle 12. For any bone marrow collected after Cycle 8 or Cycle 24, the visit may be done on Day 22-28 of that cycle.
32. A CT-PET will be performed to confirm MRD-negative disease per Standard of Care, at every time-point when MRD is checked (+/- 2 weeks). A bone marrow done as SOC 1 and 2 years after the EOT BM will be tested for MRD and a CT-PET done to confirm MRD-negative disease (+/- 2 weeks).
33. Local testing for hepatitis B surface antigen (HBsAg), hepatitis B surface antibody (Anti-HBs), and hepatitis B core antibody (Anti-HBc). HBV serology is not required at Screening if this was performed as part of standard of care within 3 months prior to first dose.
34. For subjects with serologic evidence of resolved HBV infection (i.e., positive Anti-HBs or positive Anti-HBc) at Screening, HBV DNA testing by PCR must be performed locally.
35. Q12W for up to 6 months after the last dose of study treatment.
36. If administered by subcutaneous (SC) injection, daratumumab will be provided as a fixed-dose of 1800 mg and 30,000 units hyaluronidase per 15 mL (120 mg and 2,000 units/mL) for all cycles. All subjects receiving daratumumab subcutaneous injection will be observed for at least 6 hours after the end of the SC injection during Cycle 1 Day 1 and, if deemed necessary by the treating investigator, after subsequent injections.
37. No provider patient visits will be held on Cycle 1, Day 22.

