Minimal residual disease analysis will be performed using NGS. MRD will be assessed in all bone marrow samples at the beginning of the study (after Cycles 8 and 24), yearly until progression and at any time a bone marrow biopsy is completed to assess response for suspected CR. If a CR is suspected after Cycle 8, a bone marrow biopsy and MRD testing will be completed at Cycle 12 and/or 18 to confirm. From the time CR is established, MRD analysis should continue at 12-month intervals from randomization up to 5 years in patients with ongoing sCR. The MRD samples will be evaluated by Adaptive Biotechnologies using LymphoSIGHT® platform after isolation of DNA at the University of Chicago site. For this purpose (and to establish a baseline), sites will be required to provide unstained pre-treatment slides to assess MRD status by Adaptive Biotechnologies. MRD analysis will be used only for assessment of treatment response at specified timepoints, and not for decision-making purposes.

Treatment responses will be assessed by serum free light chains (SFLC), Hevylite test, quantitative immunoglobulin levels (Igs), and serum and urine monoclonal protein starting at Cycle 2 Day 1 and at the

beginning of each subsequent cycle. Subjects with stable disease or better will continue treatment until disease progression or the development of unacceptable toxicities. All patients will then undergo a final visit (end of treatment visit).

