## 5 Patient Selection

### 5.1 Inclusion Criteria

Subjects must meet all of the following inclusion criteria to be eligible to enroll in this study. No enrollment waivers will be granted.

1. Newly diagnosed, previously untreated myeloma requiring systemic chemotherapy
  - Prior treatment of hypercalcemia or spinal cord compression or active and/or aggressively progressing myeloma with corticosteroids or lenalidomide or bortezomib-based regimens does not disqualify the patient (the treatment dose should not exceed the equivalent of 160 mg of dexamethasone in a 4-week period or not more than 1 cycle of PI/IMiD-based therapy).
2. Both transplant and non-transplant candidates are eligible
3. Diagnosis of symptomatic multiple myeloma as per current IMWG uniform criteria prior to initial treatment
4. Monoclonal plasma cells in the BM  $\geq 10\%$  or presence of a biopsy-proven plasmacytoma
5. Measurable disease, prior to initial treatment including any emergent treatment of myeloma. Measurable disease will be indicated by one or more of the following:
  - Serum M-protein  $\geq 1$  g/dL
  - Urine M-protein  $\geq 200$  mg/24 hours
  - If serum protein electrophoresis is felt to be unreliable for routine M-protein measurement, then quantitative immunoglobulin levels are acceptable

- Serum Freelite measurable disease as per current IMWG criteria
6. Bone marrow specimen will be required at study entry; available DNA sample from pre-induction BM will be used for calibration step for MRD evaluation by gene sequencing
  7. Males and females  $\geq 18$  years of age
  8. ECOG performance status of 0-1
  9. Adequate hepatic function, with bilirubin  $\leq 1.5 \times \text{ULN}$  and aspartate aminotransferase (AST) and alanine aminotransferase (ALT)  $\leq 3 \times \text{ULN}$
  10. ANC  $\geq 1.0 \times 10^9/\text{L}$ , hemoglobin  $\geq 8 \text{ g/dL}$ , platelet count  $\geq 75 \times 10^9/\text{L}$
  11. Calculated creatinine clearance (by Cockcroft-Gault)  $\geq 50 \text{ mL/min}$  or serum creatinine below  $2 \text{ g/dL}$
  12. FCBP must have 2 negative pregnancy tests (sensitivity of at least  $50 \text{ mIU/mL}$ ) prior to initiating lenalidomide. The first pregnancy test must be performed within 10-14 days before and the second pregnancy test must be performed within 24 hours before lenalidomide is prescribed for Cycle 1 (prescriptions must be filled within 7 days).

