## 5.2 Exclusion Criteria

Patients meeting any of the following exclusion criteria are not eligible to enroll in this study. No enrollment waivers will be granted.

1. Frail non-transplant candidates, defined as in Palumbo et al, Blood 2015
2. Non-secretory or hyposecretory multiple myeloma, prior to initial treatment defined as <1.0 g/dL M-protein in serum, <200 mg/24 hr urine M-protein, and no measurable disease as per IMWG by Freelite®
3. POEMS syndrome (polyneuropathy, organomegaly, endocrinopathy, monoclonal protein, and skin changes)
4. Amyloidosis
5. Plasma cell leukemia
6. Waldenström's macroglobulinemia or IgM myeloma
7. Radiotherapy to multiple sites or immunotherapy within 4 weeks before start of protocol treatment (localized radiotherapy to a single site at least 1 week before start is permissible)
8. Participation in an investigational therapeutic study within 3 weeks or within 5 drug half-lives ( $t_{1/2}$ ) prior to first dose, whichever time is greater
9. Patients not able to tolerate daratumumab, carfilzomib, lenalidomide or dexamethasone
10. Peripheral neuropathy  $\geq$  Grade 2 at screening
11. Diarrhea > Grade 1 in the absence of antidiarrheals
12. CNS involvement
13. Pregnant or lactating females
14. Major surgery within 3 weeks prior to first dose

15. Myocardial infarction within 6 months prior to enrollment, NYHA Class III or IV heart failure, uncontrolled angina, severe uncontrolled ventricular arrhythmias, or electrocardiographic evidence of acute ischemia or active conduction system abnormalities
16. Prior or concurrent pulmonary embolism
17. Known moderate or severe persistent asthma or known chronic obstructive pulmonary disease (COPD)
  - a. Known or suspected chronic obstructive pulmonary disease (COPD) with a forced expiratory volume in 1 second (FEV1) <50% of predicted normal
  - b. Moderate or severe persistent asthma within the past 2 years, or currently has uncontrolled asthma of any classification. Note that subjects who currently have controlled intermittent asthma or controlled mild persistent asthma are allowed in the study.
18. Rate-corrected QT interval of electrocardiograph (QTc) > 470 msec on a 12-lead ECG during screening
19. Uncontrolled hypertension or diabetes
20. Acute infection requiring systemic antibiotics, antivirals, or antifungals within two weeks prior to first dose
21. Known seropositive for or active viral infection with human immunodeficiency virus (HIV) or hepatitis C virus (HCV)

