|---------------------|----------------------------------------------------------------------------------------------------------------------------------------------------------------------------------------------------------------------------------------------------------------------------------------------------------------------------------------------------------------------------------------------------------------------------------------------------------------------------------------------------------------------------------------------------------------------------------------------------------------------------------------------------------------------------------------------------------------------------------------------------------------------------------------------------------------------------------------------------------------------------------------------------------------------------------------------------------------------------------------------------------------------------|
| Progressive disease | 
Increase of <math>\geq 25\%</math> from lowest response value in any one of the following:
 Serum M-component (the absolute increase must be <math>\geq 0.5</math> g/dL)and/or
 Urine M-component (the absolute increase must be <math>\geq 200</math> mg/24 h)and/or
 Only in patients without measurable serum and urine M-protein, the difference between involved and uninvolved FLC levels. The absolute increase must be <math>> 10</math> mg/dL
 Only in patients without measurable serum and urine M-protein and without measurable disease by FLC levels, bone marrow plasma cell percentage (absolute % must be <math>\geq 10\%</math>)
 Definite development of new bone lesions or soft tissue plasmacytomas or definite increase in the size of existing bone lesions or soft tissue plasmacytomas
 Development of hypercalcemia (corrected serum calcium <math>>11.5</math> mg/dL) that can be attributed solely to the plasma cell proliferative disorder
 |

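### Appendix 8 limits repeat free light chain testing to confirming CR, contradicting Sections 4.1, 6.1.2 and 6.5.2; sites that follow the calendar would have no scheduled serial values in patients measurable only by free light chains

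*Protocol*

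**What the plan says.** **Schedule of Events (Appendix 8).** The SFLC row is marked at screening, End of Cycle 4, End of Cycle 8 and End of Treatment. Each mark after screening carries footnote 19: "SFLC repeated only to confirm CR". No Day 1 is marked in any phase.

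**Section 4.1.** "Treatment responses will be assessed by serum free light chains (SFLC), Hevylite test", together with immunoglobulins and "serum and urine monoclonal protein starting at Cycle 2 Day 1 and at the" "beginning of each subsequent cycle". No subgroup limit is attached.

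**Section 6.1.2.** On Day 1 of each cycle, the tests that remain required after screening are those used to follow that patient's myeloma. The full set is required to confirm a response.

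**Section 6.5.2.** Where there is no M-spike, response in light-chain-only subjects is judged from the involved free light chain level or 24-hour total protein, at every cycle on treatment.

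**Section 6.1.3.** SFLC is listed at the end-of-treatment visit with no condition about CR.

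**Eligibility.** Section 5.1: "Measurable disease will be indicated by one or more of the following", and the list includes "Serum Freelite measurable disease as per current IMWG criteria". Exclusion 2 in Section 5.2 removes low secretors only if they also have "no measurable disease as per IMWG by Freelite".

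**Appendix 4.** The marker-based part of progressive disease uses, "Only in patients without measurable serum and urine M-protein, the difference between involved and uninvolved FLC levels". PR and VGPR in these patients are likewise defined by the fall in that difference, and CR by a normal FLC ratio.

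**The concern.** The body of the protocol and its calendar give different rules for the same test. The difference matters most for patients whose only measurable marker is the free light chain, because every marker-based response and progression category below CR depends on serial values of it.

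A site could also read the omission as deliberate. Appendix 8 makes explicit provision for patients followed by urine electrophoresis (footnotes 7, 8 and 16), for those in whom quantitative immunoglobulins replace electrophoresis (footnote 16), and for those whose only measurable disease is a plasmacytoma. It makes none for patients followed by FLC.

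At stake are secondary endpoints: overall and VGPR-or-better response rates, DOR, TTP and PFS. Section 10.2.3 plans to test all secondary endpoints against historical controls. In a single-arm comparison, progression that is found late favours the regimen, unless the historical series was assessed equally sparsely. The protocol does not say how often that series was assessed.

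**Working it through.** No statistic in the plan is being recomputed. The check sets the provisions side by side and counts time points.

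| Source | SFLC after screening |
|---|---|
| Section 4.1 | Day 1 of every cycle from Cycle 2, all patients |
| Section 6.1.2 | Day 1 of every cycle where the test is used to follow the disease |
| Section 6.5.2 | Involved FLC or 24-hour protein for light-chain-only subjects |
| Section 6.1.3 | End of treatment, unconditional |
| Appendix 8 row | End of Cycle 4, End of Cycle 8, End of Treatment |
| Appendix 8 footnote 19 | Those marks apply only to confirm CR |

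**Does the footnote belong to this row?** Yes. The lettering of the row and the footnote text agree at number 19; the numbering slips only from footnote 28 onward.

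**Are the patients eligible?** Yes. One measurable marker is enough, Freelite is one of them, and exclusion 2 does not reach them.

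**Do their categories need serial FLC?** Yes, for PR, VGPR and the marker-based limb of progression. Section 6.5.2 also asks for two consecutive assessments before progression is called.

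**Count under Section 4.1.** Day 1 of Cycles 2 to 24 is 24 − 2 + 1 = 23 on-treatment assessments, 28 days apart if no cycle is delayed.

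**Count under Appendix 8.** There are three marks, each conditional on confirming CR. A patient in whom CR is never suspected therefore has no scheduled SFLC under the footnote.

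**Most generous reading of Appendix 8.** Suppose the three marks are mandatory. For a patient who completes Cycle 24, End of Cycle 8 to the end of Cycle 24 is 16 × 28 = 448 days. Adding about 28 days to the end-of-treatment visit gives about 476 days without a scheduled value, against 28 days under Section 4.1.

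**Direction of the effect.** Later detection of biochemical progression lengthens TTP and PFS, and it lengthens DOR at its end. A PR or VGPR that is never recorded lowers the response rates; one recorded late moves the start of DOR, which offsets part of the lengthening.

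**The case against.** The strongest reply is that the protocol already provides for the measurement. Three body sections (4.1, 6.1.2 and 6.5.2) lead to FLC at each cycle in these patients, and 6.1.3 requires it at end of treatment. Section 6 points to Appendix 8 for an overview, and the grid is visibly incomplete: it has no row for Hevylite, quality of life or echocardiogram, all of which the body requires. On this view a single footnote should not be read as overriding the sections.

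Much of that stands, and it makes the consequence conditional: it arises only where a site works from the calendar. It does not remove the contradiction. The word *only* restricts testing rather than deferring to the text, and no clause in the protocol says which prevails.

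Three stronger readings are tempting, and the documents do not support them:

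- **That response and progression in these patients would simply go unmeasured.** The body sections order the test. Progression is also defined by bone lesions, plasmacytomas and hypercalcaemia, none of which depend on FLC.
- **That CR might never be suspected.** Serum and urine immunofixation continue on Day 1 in every phase, and marrow is taken from all subjects at the end of Cycles 8 and 24. A suspected CR triggers a complete assessment that includes SFLC.
- **That a known number of patients is affected.** An assumed share of 10% to 20% of 45 would be 4.5 to 9 patients, but nothing in the protocol supports that range.

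**Conclusion.** The contradiction is real and should be corrected. Footnote 19 and the SFLC row cannot be followed together with Sections 4.1, 6.1.2 and 6.5.2. Under the calendar, patients measurable only by Freelite have no scheduled serial FLC between screening and either a suspected CR or end of treatment. PR and VGPR could then be missed, and biochemical progression dated late.

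The exposure is confined to secondary endpoints. The primary sCR assessment at the end of Cycle 8 is largely unaffected because SFLC is still done to confirm CR, and the NGS result for MRD does not use it.

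The size rests on two things the protocol does not give: how many patients are measurable only by FLC, and how many sites follow Appendix 8 rather than the body text. The scheduling gap can be counted (23 assessments against three conditional ones); its effect on the results cannot.

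**What to change.** - Delete the word *only* from footnote 19 and bring the footnote and the SFLC row into line with Sections 4.1, 6.1.2 and 6.5.2.
- Mark SFLC on Day 1 of each cycle from Cycle 2, at least for patients whose disease is followed by FLC.
- For all patients, mark it at any suspected CR or better and at end of treatment, as Sections 6.1.2 and 6.1.3 already require.
- State which rule governs the remaining patients. Section 4.1 covers everyone; Section 6.1.2 covers only those in whom the test is used to follow the disease. If 6.1.2 is meant, amend 4.1 to say so; otherwise the two body sections will still disagree after the appendix is corrected.

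The cost is one footnote, one grid row and possibly one sentence in Section 4.1. No testing is added beyond what Section 4.1 already orders. Section 6.3.5 indicates that patients were already on treatment when this version was written, so a listing of actual SFLC dates for patients measurable only by FLC would show whether any gap has occurred.
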